## Abstract

**Background:**

In South Africa, pregnant and lactating women (PLW) face a dual burden of high alcohol use and HIV prevalence, both of which adversely affect maternal and infant health. However, few interventions address alcohol use and HIV risk concurrently in this population.

**Objective:**

This study seeks to adapt and pilot-test in a randomized controlled trial (RCT) the peer-led multisession intervention Mentor Mothers Plus (MM+) to integrate alcohol reduction strategies with HIV prevention and care support (in a seroneutral intervention) among PLW in Saldanha Bay, Western Cape, South Africa.

**Methods:**

Using the ADAPT-ITT (assessment, decision, adaptation, production, topical experts, integration, training, testing) framework, we adapted the evidence-based Mentor Mother (MM) model, originally aimed at reducing vertical HIV transmission among mothers with HIV. Our mixed methods design includes (1) qualitative research, including in-depth interviews (IDIs) and focus group discussions (FGDs), to assess drivers of perinatal alcohol use and HIV risk; (2) intervention adaptation through community-based participatory workshops with stakeholders to refine the MM+ intervention in order to include culturally and contextually strategies; and (3) a pilot RCT with 100 pregnant women (≥16 years old, reporting recent alcohol use) randomized in a 1:1 ratio to the MM+ intervention (motivational interviewing [MI], including HIV and alcohol reduction messaging) or enhanced standard of care (SOC). Primary RCT outcomes include reduced alcohol use, via phosphatidylethanol (PEth) blood levels at 6-month follow-up. Secondary outcomes include uptake and adherence to pre-exposure prophylaxis (PrEP) and antiretroviral therapy (ART) among women with HIV, as well as intervention fidelity, feasibility, and acceptability.

**Results:**

Community research included 2 FGDs with health workers (n=6) and community leaders (n=7) and 31 interviews with partners and peers of PLW. Data showed that women are motivated to reduce alcohol use for child health but face barriers (eg, misconceptions about safety of alcohol use, poverty, trauma, and intimate partner violence [IPV]). Alcohol use is with friends/family members/partners and tied to financial stress, unplanned pregnancy, and poor mental health. MM+ support preferences emphasize nonjudgmental, peer-based mentorship, family involvement, and faith/community engagement. Gaps include stigma around HIV and contraceptive services. Communities recommend mentor mothers with lived experience, providing culturally relevant, empathetic support, and linking to social and clinical services. In August 2025, a community workshop refined the intervention, emphasizing the need for trustworthy mentor mothers with lived experience. Priorities included culturally relevant information on alcohol use, HIV prevention, family planning, trauma and interpersonal violence support, and flexible delivery. Next steps involve finalizing materials, training mentor mothers, and launching the RCT.

**Conclusions:**

Our community-based, participatory study, MM+, offers a promising approach to address co-occurring alcohol use and HIV among PLW. Stakeholder engagement enhances contextual relevance and supports future scalability. The RCT will evaluate efficacy of the model in reducing alcohol and improving HIV outcomes.

**Trial Registration:**

Clinicaltrials.gov NCT06962592; https://clinicaltrials.gov/study/NCT06962592

**International Registered Report Identifier (IRRID):**

DERR1-10.2196/78856

## Introduction

### Background

South Africa bears the highest global burden of both alcohol use during pregnancy and HIV prevalence. [1-3]. These interlinked public health crises are particularly concerning for pregnant and lactating women (PLW) due to their compounded impact on maternal, fetal, and child health. In the Western Cape province in South Africa, alcohol use during pregnancy is prevalent, contributing to some of the world’s highest rates of fetal alcohol spectrum disorder (FASD), with estimates ranging from 64 to 310 per 1000 live births [4,5]. Further, breastfeeding while consuming alcohol can impair child neurodevelopment, emphasizing the need for intervention throughout the perinatal period [6].

Pregnancy and postpartum are also periods of heightened risk for HIV, with the likelihood risk of acquisition more than doubling during this time [7]. Recent formative work among pregnant women at risk of HIV in Cape Town found that pregnant women who engage in alcohol use are more likely to report having recent condomless sex and multiple sex partners [8]. Qualitative work contextualized these findings, suggesting that alcohol use, HIV risk behaviors, nonadherence to HIV treatment, and experiences of intimate partner violence (IPV) are all inextricably linked health issues [9,10]. Despite the Joint United Nations Programme on HIV/AIDS (UNAIDS) and the World Health Organization’s (WHO) 2025 targets to eliminate vertical HIV transmission (defined as <2% HIV transmission or <50 cases per 100,000 live births) [11], South Africa’s pediatric HIV incidence still exceeds 750 per 100,000 live births. This is largely driven by a 30% antenatal HIV prevalence [11]. Considering the high HIV incidence in pregnancy, access to oral and other forms of pre-exposure prophylaxis (PrEP) are essential for PLW who do not have HIV [12,13], while women with HIV must be on and adhere to antiretroviral therapy (ART) to mitigate vertical HIV transmission [14-16]. However, alcohol use interferes with HIV care engagement, delaying ART initiation, reducing adherence, and ultimately increasing the risk of vertical HIV transmission [14-17]. Given the evidence that alcohol use disrupts biomedical HIV prevention and treatment, adherence-targeted interventions are critical.

Despite these risks, community-informed interventions targeting both HIV and alcohol use among PLW are lacking. The few existing brief interventions targeting alcohol use during pregnancy have shown limited effectiveness, in part due to short follow-up periods and the absence of biomarker validation [18,19]. Integrating peer mentor mothers into existing care structures is one promising evidence-based approach that has improved maternal health outcomes and reduced vertical HIV transmission in South Africa [20,21]. The existing Mentor Mother (MM) intervention, implemented by peer mothers to mothers, leverages task shifting, where positive deviant peer mothers provide counseling and support, typically through home-based delivery. The prior models have focused mostly on prevention of vertical HIV transmission but do not include any messaging on alcohol or substance use reduction. The previous interventions have been successfully adapted to address broader maternal-child health outcomes in Africa and have shown promise in reducing alcohol use [22]. However, alcohol has never been the primary focus of MM intervention content. Guided by ADAPT-ITT (assessment, decision, adaptation, production, topical experts, integration, training, testing), a framework developed to systematically adapt evidence-based HIV interventions, our study seeks to adapt the MM approach to reduce alcohol use and improve HIV prevention and treatment outcomes among PLW in South Africa [23].

Brief interventions for alcohol use in pregnancy have shown limited effectiveness. Although interventions such as the Philani Program Plus (an MM model) have shown reduction in alcohol use over extended periods, achieving early abstinence remains challenging [24]. Our study aims to bridge these gaps by integrating motivational interviewing (MI) techniques to assist with reduction in alcohol or other substance use through peers with lived experience of being pregnant and reducing or stopping alcohol use during pregnancy and breastfeeding.

The MM approach is well suited for this context, offering a cost-effective, accessible, and scalable approach through leveraging existing community health worker structures [25-27]. The model is highly adaptable, having been successfully implemented to address diverse health challenges across Africa, including HIV, nutrition, and child development [28,29]. The approach has also demonstrated effectiveness, producing significant reductions in vertical HIV transmission and improved ART adherence [27,30]. In addition to this approach, to further enhance the intervention impact, we will integrate MI—another evidence-based strategy shown to reduce alcohol use among PLW—into our adapted MM model [19,31].

### Theoretical Approach: Theory-of-Change Framework

Given the sociocultural complexities of alcohol use and HIV risk among PLW in South Africa, identifying a theory of change is critical to understanding the causal pathways that drive these behaviors and designing a responsive intervention [32]. The theory of change is an outcomes-based approach to understanding health behavior that maps how and why change occurs, articulating causal linkages between activities, outcomes, assumptions, and contextual factors [33].

The theory-of-change model identifies the multilevel determinants influencing alcohol use and HIV risk among PLW, including individual (eg, stress, depression), interpersonal (eg, intimate partner violence [IPV], peer influence), and community (eg, social norms, poverty) factors [34-36]. Key components of this framework include long-term (reduced maternal alcohol use, improved HIV prevention behaviors, and decreased vertical HIV transmission), intermediate (improved alcohol use disclosure, increased uptake and adherence to PrEP/ART, and reduced stigma in accessing care), and immediate (increased knowledge and motivation to reduce alcohol use, improved access to health services, and strengthened peer and community support systems) outcomes.

## Methods

### Study Design

This study was registered at ClinicalTrials.gov (NCT06962592, v1.0). The study is being implemented in Saldanha Bay, located in Western Cape, South Africa, which has a high burden of HIV and PLW who use alcohol. This periurban/rural fishing community has a population of over 150,000 people. The prevalence of FASD in the area was 64 children per 1000 affected (6.4%) in 2014—one of the highest rates worldwide [11].

The study location (Figure 1) presents unique context where Black and mixed-race women in South African communities face a confluence of social and structural challenges that exacerbate the risk of perinatal alcohol use and HIV [37]. A legacy of the apartheid era, the *dop* system—where laborers were paid with alcohol—contributed to a culture of heavy alcohol use, further reinforced by informal local bars, called *Shebeens*. Given the significant contextual and cultural drivers of alcohol use in PLW in this setting, we will prioritize community input and coadaptation of the intervention to optimize intervention fit and relevance.

**Figure 1 figure1:**
[figure not shown]
Map of the West Coast region, South Africa.

This work is being carried out in partnership with the Foundation for Alcohol-Related Research (FARR), which has a longstanding community service presence in Saldanha Bay since 2012. We are leveraging this strong community presence to facilitate reaching this hard-to-reach population, build trust, and deliver services in a way that is responsive to their needs and grounded in longstanding local relationships**.**

### Study Aims and Approach

The study aims (Figure 2) are as follows:

**Figure 2 figure2:**
[figure not shown]
Study research aims and activities mapped on the ADAPT-ITT and theory-of-change frameworks. FGD: focus group discussion; IDI: in-depth interview.

Assess the drivers of perinatal alcohol use from the perspective of key individuals who influence behaviors (drinking peers, intimate partners, community leaders, health care providers) through a mixed methods assessment to identify barriers to and facilitators of alcohol use reduction.Adapt the MM model by collaborating with stakeholders and refining the “Mentor Mothers Plus” (MM+) intervention, integrating culturally and contextually appropriate alcohol reduction strategies.Evaluate the intervention’s feasibility and acceptability by conducting a pilot randomized controlled trial (RCT) with 100 PLW using alcohol and determine the intervention’s preliminary impact on alcohol use and HIV prevention and treatment behaviors.

### Qualitative Research

We conducted in-depth interviews (IDIs) with partners, as well as peers and family members of pregnant women who drink alcohol. We also conducted focus group discussions (FGDs) with health care and community stakeholders to assess the drivers of perinatal alcohol use from the perspective of key individuals who influence behaviors. We have completed IDIs and FGDs with PLW previously [9,10]. We conducted concurrent mixed methods research with key stakeholders of PLW who use alcohol to explore facilitators of continued alcohol use in pregnancy at the interpersonal, community, and health care facility levels, with the aim of identifying and assessing intervention needs and opportunities (step 1 of ADAPT-ITT).

#### Inclusion Criteria (Formative Stage)

We identified intimate partners and drinking peers (drinking partners, who include friends and family members) of PLW to examine interpersonal and social facilitators of alcohol use while pregnant. In addition, we engaged health care providers working with PLW (nurses, midwives, and HIV counselors) and local leadership (influential community and religious figures) in FGDs to identify facility-, provider-, and community-level barriers to addressing alcohol use in this population (Table 1).

**Table 1 table1:** Description of the purpose, sample, and content of data collection in aim 1 of the MM+^a^ study.

Study methods	Population: intimate partners and peers	Health care population: health care providers and community leaders
Purpose	Understand interpersonal factors contributing to alcohol use among PLW^b^ Understand how alcohol use and HIV risk intersect among PLW Identify support from partners or peers Identify points of intervention	Assess how maternal health care providers address alcohol use in pregnancy as well as access to HIV prevention and care services Identify points of intervention
Sample	Drinking partners (n=15) Intimate partners (n=15)	Health care workers (k=1, n=8) Community and religious leaders (k=1, n=8)
IDIs^c^/FGDs^d^	Firsthand experience of using alcohol with PLW or peers Perceptions of alcohol use in pregnancy Perceived facilitators and barriers to reducing alcohol use in pregnancy Other HIV risk behaviors	Perspectives on alcohol use among PLW Current interventions to address alcohol use among PLW (for providers) Facilitators and barriers to reducing alcohol use in pregnancy and HIV intervention uptake in PLW
Survey measures	Sociodemographic data	—^e^

^a^MM+: Mentor Mothers Plus.

^b^PLW: pregnant and lactating women.

^c^IDI: in-depth interview.

^d^FGD: focus group discussion.

^e^Not applicable.

Trained researchers conducted semistructured IDIs and FGDs using interview guides in Afrikaans and English. All materials were drafted in English and translated into Afrikaans by experienced team members. Data collection for this aim includes (1) semistructured IDIs with drinking and intimate partners of PLW who use alcohol, (2) FGDs with health care providers and community leaders, and (3) concurrently collected brief surveys administered to IDI participants to gather sociodemographic and behavioral data, including perceptions and practices regarding alcohol use during pregnancy (eg, proportion of providers assessing alcohol use at visits, proportion of partners supportive of alcohol use during pregnancy). For qualitative analysis, we will focus on salience-based saturation [38], identifying key themes mentioned by two or more participants.

FARR community-based staff used purposive sampling and snowball sampling for recruitment of drinking partners and intimate partners of PLW who use alcohol. Data collectors received training on sensitive interviewing dealing with distressed participants and referrals.

#### Eligibility Criteria and Key Informant Recruitment

Health care providers were purposively selected from Saldanha Bay municipality clinics and the Vredenburg Provincial Hospital. Community leaders were recruited with help from our Community Advisory Board (CAB), clinic staff, government leaders, social workers, and FARR. An IDI participant must identify as an intimate partner, friend, or family member of a PLW who used alcohol during pregnancy. Participants include adults (≥18 years old) in professional or community roles related to HIV care, maternal health, or alcohol use or in community roles, such as elders, members of faith-based organizations, or civil society representatives, able to provide informed consent. For IDIs with partners, friends, and family members, participants included adults (≥18 years old) living in the study community who reported drinking with a pregnant woman now or in the past. Recruitment was facilitated by the community-based partner through local networks and snowball referrals.

IDIs and FGDs were held in private community spaces or at FARR offices to ensure confidentiality. Participants were reimbursed for their time, inconvenience, and expenses they may have incurred due to being interviewed, with a grocery voucher for a local store. For the FGDs and IDIs, we used rapid qualitative analytic methods. Audio recordings, detailed notes, and transcripts were reviewed by researchers trained in qualitative methods (authors DD and ZP) and fluent in Afrikaans. Data review followed a structured extraction template organized around key domains relevant to intervention adaptation (eg, experiences of people living with HIV [PLWH], provider perspectives, and contextual barriers and facilitators). Data were then transcribed and translated, and two additional analysts (authors ZE and AM) independently populated the template as second reviewers, after which findings were reconciled to resolve discrepancies. The reconciled data were then summarized and cross-checked by the broader study team, including study leadership, to ensure analytic rigor and validity. Extracted data were examined for consistency, key themes, and areas requiring clarification, with opportunities for member checking with community participants to enhance credibility. The resulting thematic findings informed the content presented in the consensus-building workshop and guided adaptation of the intervention.

#### Community Workshop

We applied the community-based participatory action research (CBPAR) principles through three sequential activities to refine and adapt the MM model:

Adaptation of the MM model through collaborative consensus-building workshop. In August 2025, we conducted a collaborative consensus-building workshop with 29 stakeholders in Saldanha Bay to adapt the MM model (step 3 of ADAPT-ITT). Formative findings from aim 1 and the essential components of the existing MM model (content and literature) were reviewed in a participatory 1-day workshop with health care providers, social workers, civil society, women with lived experience, and community leaders recruited by FARR. The workshop was cofacilitated by the study team with FARR, in both English and Afrikaans, depending on participants’ preferences. Feedback and comments were used to collaboratively adapt key components of the intervention. The study staff obtained consent from participants using English or Afrikaans consent forms. Participants were reimbursed for the time, travel, and expenses. Following the workshop, the adapted MM+ intervention will be iteratively pilot-tested (steps 4-6 of ADAPT-ITT).Development of draft MM+ model (August-December, 2025). The research team will use the updated draft intervention and qualitative findings from the workshop to produce a draft ready for pilot-testing among pregnant women and develop study materials, including consent materials, standard operating procedures (SOPs), monitoring and evaluation indicators and tools, and research related instruments (survey and SOPs for blood tests) in preparation for piloting of the MM+ intervention in aim 3.

#### Analytic Approach

We applied rapid qualitative analysis methods for the consensus-building workshop. Notes were reviewed by trained researchers to capture key points from group discussions. Participants focused on core intervention components: who should be included, what content to address, where sessions should take place, and how/when delivery should occur. Each group presented its recommendations to the larger workshop, where ideas were compared and discussed to identify approaches most appropriate for the community context [39,40]. We used findings to inform adaptation of the MM model and development of finalized manuals for the pilot study.

### Study Design for the Pilot RCT (January 2026-February 2027)

We will identify and train 3-5 mentor mothers from the community. Inclusion criteria for mentor mothers include women (≥25 years old) in the community with lived experience who are either on PrEP or have HIV and are on ART and who reported reducing or stopping using alcohol during pregnancy. Mentor mothers will be trained on the adapted MM+ curriculum and MI techniques (step 7 of ADAPT-ITT). We will include 10-15 providers (midwives, nurses, and counselors) to be part of the MM+ training and support the integration of MM+ in three antenatal care (ANC) clinics. Concomitant ante- and postnatal care, including HIV testing and ART and PrEP provision, will be provided to all women regardless of study allocation.

Following training, trained study staff in three local clinics and surrounding communities will recruit and enroll 100 pregnant women who report recent (past 2 months) alcohol use to evaluate the effectiveness and feasibility of the MM+ intervention in reducing alcohol use in PLW, PrEP use in PLW without HIV, and ART adherence in PLW with HIV (step 8 of ADAPT-ITT). Participants will be randomized in a 1:1 ratio to the MM+ study arm or enhanced standard of care (SOC). SOC is focused on HIV counseling by peers, without alcohol messaging. If we are unable to identify 100 women in the three select clinics and communities, we will expand to additional communities and clinics.

### Description of the MM+ Intervention

MM+ will involve mentor mother delivery of brief MI sessions individually over a series of clinic-based visits over a 6-month period during pregnancy and postpartum. Although the exact number of mentor mother sessions, the finalized intervention content, and the full menu of HIV prevention services offered will be finalized during the community workshop, based on the dose from previous MI RCTs in South Africa [41,42], we anticipate no fewer than five to six 15-20–minute MI sessions focused on the benefits of reducing alcohol use during pregnancy and managing HIV risk among women without HIV and the importance of ART use and viral suppression for reducing the risk of vertical HIV transmission. Participants in both study arms will receive enhanced HIV prevention counseling integrated into routine ANC visits, including PrEP and ART biofeedback adherence using urine tenofovir (TFV) tests that are point-of-care inexpensive tests that provide feedback on the recent use of PrEP or ART in the past 72-hours [43-45]. In the intervention arm, these services will be provided by a trained study nurse. See Figure 3 for a breakdown of the anticipated intervention structure.

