### Enhanced Standard of Care

Given that existing MM models focus on vertical HIV transmission and HIV prevention and treatment, and our primary aim is to understand how inclusion of alcohol reduction strategies reduces alcohol use and improves adoption of ART/PrEP use, we will use enhanced SOC with the same time frame for the intervention (eg, two to three sessions during antenatal and two to three sessions during postpartum periods). This will consist of educational counseling delivered by peers (mentor mothers) on HIV risk, partner testing modalities, and PrEP/ART urine assay testing, followed by real-time in-clinic adherence counseling delivered privately (one on one) by mentor mothers (separate from intervention mentor mothers to avoid contamination), all coinciding with routine ANC visits when possible.

Benefits of the study include counseling and support from lay counselors (in SOC) and mentor mothers (in the intervention) to address alcohol use and HIV prevention and care. Risks include unintended disclosure of alcohol use or HIV status by providers or staff and potential breaches of confidentiality that could cause social harms, including IPV. We will train staff and providers to ensure they are aware of these risks and do not share details of participants’ status outside of the study. We will monitor all social and other study harms throughout the study through regular surveys and review of medical records.

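### HIV counselling and urine feedback meant for both arms come from a nurse in MM+ and from peers in control, so the adherence contrast cannot isolate the alcohol component; the control-arm text also conflicts on content and deliverer

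*Protocol article*

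**What the plan says.** All references are to the Protocol article.

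- **A component common to both arms.** Description of the MM+ Intervention: "Participants in both study arms will receive enhanced HIV prevention counseling integrated into routine ANC visits, including PrEP and ART biofeedback adherence".
- **Deliverer in MM+.** The same paragraph continues: "In the intervention arm, these services will be provided by a trained study nurse".
- **Deliverer in control.** Enhanced Standard of Care has peers counsel on several topics, the urine test for PrEP/ART among them. This is then "followed by real-time in-clinic adherence counseling delivered privately (one on one) by mentor mothers (separate from intervention mentor mothers to avoid contamination".
- **The question to be answered.** Same section: "our primary aim is to understand how inclusion of alcohol reduction strategies reduces alcohol use and improves adoption of ART/PrEP use".
- **Control content, design statement.** Study Design for the Pilot RCT: "SOC is focused on HIV counseling by peers, without alcohol messaging".
- **Control content, benefits statement.** The second paragraph of Enhanced Standard of Care lists as benefits "counseling and support from lay counselors (in SOC) and mentor mothers (in the intervention) to address alcohol use and HIV prevention and care".
- **Shared clinic staff.** Study Design for the Pilot RCT: "We will include 10-15 providers (midwives, nurses, and counselors) to be part of the MM+ training". The same paragraph says that ante- and postnatal care goes to all women whatever their allocation.

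RCT Outcomes makes the change in PEth from baseline to 6 months the primary outcome. PrEP initiation and adherence and ART adherence, measured with urine TFV testing among other sources, are secondary.

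**The concern.** To learn what the alcohol component adds, everything else should be the same in both arms. The HIV counselling and urine feedback are described as common to both, yet their deliverer changes with randomisation. They also act directly on the behaviour that the secondary outcomes measure. If TFV-based adherence is better in MM+, the trial cannot say whether the alcohol content helped or whether women responded differently to a nurse than to a peer. If adherence is no better, a benefit of one could be hidden by a disadvantage of the other.

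The control-arm contradiction is a separate matter. Staff need one answer to whether control sessions touch on alcohol, and readers of the PEth result need to know what MM+ was compared with.

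**Working it through.** The plan states no figure on this point, so the check is a comparison of the texts.

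**1. Deliverer of the HIV component, by arm**

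| Element | MM+ arm | Control arm |
|---|---|---|
| Adherence counselling and urine TFV feedback | trained study nurse (Description of the MM+ Intervention) | mentor mothers (Enhanced Standard of Care, first paragraph) |
| Mentor-mother motivational sessions with alcohol content | yes | no, by the design statement |
| Collection of the urine sample | study staff (Outcome Data Ascertainment) | study staff (same section) |

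Two rows differ between arms. Only the second is the difference that the stated aim is about.

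**2. What the adherence contrast estimates**

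Let A be the effect on adherence of the motivational sessions that carry the alcohol content. Let C be the effect of nurse rather than peer delivery of the HIV component, in the presence of those sessions. The trial observes D = A + C. D equals A only if C = 0, and the document gives no ground for assuming that. Every MM+ woman has the nurse and every control woman has the peer, so indicators for arm and for deliverer would be the same column in any regression. Covariate adjustment, subgroup analysis and imputation cannot split D. No value for C can be taken from the document, so the point has a direction of doubt but no numerical size.

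**3. Reach across outcomes**

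- *TFV-based PrEP and ART adherence:* direct, because the differing component is adherence counselling.
- *PEth:* indirect. The nurse's stated task is HIV counselling and feedback, and any effect on drinking would have to come through that contact.

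**4. Control-arm descriptions side by side**

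| Place | Who delivers | Alcohol content |
|---|---|---|
| Study Design for the Pilot RCT | peers | none |
| Enhanced Standard of Care, first paragraph | mentor mothers | none listed |
| Enhanced Standard of Care, benefits sentence | lay counselors | included, if read literally |

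The benefits sentence departs from the other two on content. It also contrasts lay counselors with mentor mothers, although the paragraph before it assigns the control sessions to mentor mothers.

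**5. Shared clinic staff**

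Randomisation is by individual woman (RCT Inclusion Criteria). The stated safeguard against contamination is a separate set of mentor mothers. It does not cover MM+-trained clinic providers, who also see control women. The article describes no measure of alcohol counselling received outside the study sessions.

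**The case against.** The strongest reply is that randomisation still gives an unbiased comparison of MM+ as delivered with control as delivered. If the nurse belongs to the package, an adherence difference is properly credited to the package. This stands. What is lost is attribution to the alcohol component, and the article itself names that as its aim.

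Four stronger readings are tempting, and the document does not support them.

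- *The outcome measurement itself differs by arm.* It is not shown to. Outcome Data Ascertainment has study staff take the urine at each visit with no distinction by arm, and prescriptions and viral loads come from medical files or the national laboratory.
- *Control women receive alcohol counselling.* Only the benefits sentence suggests it. That sentence pools the benefits of both arms and may be loosely worded, while the design statements describe an HIV-only control.
- *Contact time is unequal.* Control has 2 to 3 antenatal plus 2 to 3 postpartum sessions, so 4 to 6 in all, against at least 5 to 6 sessions in MM+. No control session length or nurse contact time is given, and the figure showing the arm structure is not available here. Inequality is possible but not established.
- *Contamination through trained clinic staff costs a calculable amount of power.* Providers are to join the training and support integration. The article does not say that they will counsel control women on alcohol. Any power figure would need an assumed contamination rate and an assumed effect in contaminated women, so none is given.

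It is also fair to say that this is a pilot seeking preliminary impact, and that the deliverer mismatch bears mainly on secondary outcomes.

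**Conclusion.** The point holds in two limited parts.

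First, as written, the TFV-based PrEP/ART adherence contrast combines the alcohol content with nurse versus peer delivery and cannot isolate the former. This follows from the text alone and assumes only that both deliverer statements are meant literally. The intention-to-treat comparison of the packages is unaffected. The PEth comparison is touched only indirectly, and it would be wrong to conclude that the primary contrast is invalid.

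Second, the descriptions of the control arm contradict each other on deliverer and on alcohol content. This is unresolved wording, not evidence that controls receive alcohol counselling.

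Both parts should be settled before launch, because once women are enrolled under different deliverers the adherence contrast cannot be repaired in analysis.

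**What to change.** 1. Reconcile Description of the MM+ Intervention with Enhanced Standard of Care, so that the HIV counselling and TFV biofeedback are delivered by the same cadre with the same script in both arms. Which cadre is the sponsor's choice. If the difference is intended, state that the adherence contrast estimates the effect of the whole package and not of the alcohol component.
2. Reconcile Study Design for the Pilot RCT with both paragraphs of Enhanced Standard of Care into one statement of who delivers the control condition and whether it has alcohol content.
3. Because MM+-trained clinic providers also serve control women, add one item to the existing 6-month survey in both arms: was alcohol counselling received, and from whom? Contamination can then be described rather than guessed at.

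The cost is protocol wording, one survey item and, if the cadre is aligned, some reallocation of existing staff time. The provider training can go ahead as planned. Postponing it would work against the pilot's own aims of clinic integration and provider-rated feasibility.
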